### Criteria for discontinuing or modifying interventions {11b}

After allocation to the experimental or control arm, the patient can still be excluded from the study in certain cases, specified as the perioperative exclusion criteria. A patient allocated to the control arm may be excluded if there is a clear indication for hypersensitivity reactions to commercially available fibrin sealants. Patients allocated to L-PRF may be excluded if the L-PRF preparation process fails or if the product is considered of insufficient quality. Subjects with other intraoperative findings identified by the surgeon that may preclude the conduct of the study procedure can be excluded as well, to ensure optimal patient care in the situation. For example, when the dura is exceptionally damaged, the surgeon may opt for multilayer reconstruction using multiple grafts, commercially available sealants, and autologous materials. Study participants can withdraw from the study at any moment, which implies all subsequent study procedures and data collection are discontinued.

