### Sample size {14}

Sample size calculation was performed according to the primary outcome, using an online power calculator for binary outcome non-inferiority trials (Sealed Envelope Ltd. available from: www.sealedenvelope.com). This is a non-inferiority trial with a binary outcome using a one-sided alpha of 0.05 and 80% power. The assumed success rate is 93.7% in the control arm, based on center-specific experience as well as the literature [13]. Data on the use of L-PRF for this indication is limited, but we assume a 95% success rate based on a prior feasibility study [9].

The statistical hypothesis for testing the treatment difference is presented as follows: H_0_: Δ ≤  − 0.05 tested against the alternative hypothesis and H_A_: Δ >  − 0.05, where Δ is the difference between the success rates of experimental and control condition and − 0.05 is the non-inferiority difference. The non-inferiority limit was set at 0.05 considering (1) reported CSF leakage rates without commercially available fibrin sealant averaging 17.2% [14] and (2) important additional benefits of L-PRF compared to commercially available fibrin sealants including the completely autologous nature (eliminating immune reactions), presence of immunologic cells and reduced costs.

Based on this power calculation, 334 patients need to be included, 167 in each group. A drop-out rate of 2–5% is expected due to loss of follow-up and non-adherence to the allocation or failure of L-PRF preparation. Therefore, 350 patients will be enrolled, 175 in each group.

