#### Plans to promote participant retention and complete follow-up {18b}

The 6–12 weeks postoperative outpatient follow-up (FU3) is planned and notified to the patient before hospital discharge. Patients are requested to fill in the questionnaires at the 6–12 weeks postoperative visit (FU3). If the patient is not present at this appointment, or if the clinical follow-up appointment is rescheduled outside the FU3 visit time window (6–12 weeks postoperative), the patient is contacted by telephone to complete the questionnaires within the proposed time window. If this attempt is unsuccessful, the patient is considered lost to follow-up. In case of subject withdrawal, an exit note is added to the electronic case report form (e-CRF) mentioning the withdrawal date and reason of withdrawal.

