### Methods in analysis to handle protocol non-adherence and any statistical methods to handle missing data {20c}

The results will be analyzed according to the “intention-to-treat” (all randomized participants, irrespective of protocol adherence), “per-protocol” (only participants that were treated according to the protocol), and “as-treated” (all participants according to the treatment they received) principles. These three analyses will be compared to show the possible impact of a lack of data on the results. For the primary endpoint, no missing data are expected. For secondary endpoints (cost-effectiveness evaluation), the predictive mean of the other values within the arm will be used.

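### The plan expects no missing primary outcomes, yet it sizes the trial for loss to follow-up and ends data collection at withdrawal, and its stated check cannot show the effect of missing outcomes

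*Protocol article*

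**What the plan says.** Section {20c} states: "For the primary endpoint, no missing data are expected". It defines the intention-to-treat set as everyone randomised. It names per-protocol and as-treated sets as well, and says that comparing the three will show how a lack of data could affect the results. It gives an imputation rule for secondary endpoints only.

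Other sections of the same article expect losses:

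- Sample size {14}, which is calculated on the primary outcome: "A drop-out rate of 2–5% is expected due to loss of follow-up and non-adherence to the allocation or failure of L-PRF preparation". The required number is given as "334 patients need to be included, 167 in each group", and then: "Therefore, 350 patients will be enrolled, 175 in each group".
- Discontinuation criteria {11b}: a participant may withdraw at any time, "which implies all subsequent study procedures and data collection are discontinued".
- Retention {18b}: a patient who misses the FU3 window is telephoned to complete the questionnaires. "If this attempt is unsuccessful, the patient is considered lost to follow-up". The section does not say that leak status is asked on that call.

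**The concern.** Sections {14} and {11b} each describe a route by which a randomised patient can reach week 12 with leak status unknown, while {20c} says there will be no such patients. An intention-to-treat analysis of everyone randomised cannot be carried out for a patient with an unobserved outcome unless a counting rule exists, and the sentence in {20c} removes the reason to have one.

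The substitute check does not fill the gap. Moving a patient between the intention-to-treat, per-protocol and as-treated sets changes the arm in which the patient is counted, or whether the patient is counted at all, according to the treatment given. It says nothing about what the unobserved outcome might have been. The three results could agree closely and still all depend on the same unstated handling of missing leak status.

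The trial expects few events and has a 5-point margin, so the handling of a few patients can decide whether non-inferiority is declared.

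**Working it through.** **Inputs.** From {14}: success 93.7% (control) and 95% (L-PRF), margin 0.05, "using a one-sided alpha of 0.05 and 80% power", 167 per arm required, 175 per arm enrolled, drop-out 2–5%. From {20a}: a two-sided 95% interval for the risk difference. The one-sided 0.05 test corresponds to the lower 90% limit, so both limits are shown.

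**1. Reproduce the plan's figure.** With unpooled variance, n per arm = [p₁(1−p₁) + p₂(1−p₂)] × (1.645 + 0.842)² / (margin + p₂ − p₁)². The variance term is 0.937×0.063 + 0.95×0.05 = 0.1065 and the denominator is 0.063². The result is 165.9, so 166 per arm against the stated 167. Inflating 334 for drop-out gives 341 at 2%, 350 at 4.5% and 352 at 5%. The stated figures hold. The allowance is 350 − 334 = 16 patients, or 4.6%.

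**2. Drop-outs against expected events.** Leaks among 350: 175×0.063 + 175×0.05 = 11.0 + 8.75 = 19.8. Drop-outs: 350×0.02 = 7 and 350×0.05 = 17.5.

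| Drop-out | Patients | As share of 19.8 leaks |
|---|---|---|
| 2% | 7 | 35% |
| Plan's allowance | 16 | 81% |
| 5% | 17.5 | 88% |

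**3. What the counting rule can do.** Assumptions for illustration: outcomes are missing equally in both arms, observed patients leak at the planning rates, and limits are Wald limits on the difference in success (L-PRF minus control). The margin is −0.05. Each cell gives the lower 95% limit, then the lower 90% limit.

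| Missing per arm | Complete cases | All missing = success | All missing = leak | Extreme: L-PRF leak, control success |
|---|---|---|---|---|
| 1% (1.75) | −0.036 / −0.028 | −0.035 / −0.028 | −0.039 / −0.031 | −0.047 / −0.039 |
| 2% (3.5) | −0.036 / −0.028 | −0.035 / −0.028 | −0.043 / −0.034 | −0.059 / −0.051 |
| 5% (8.75) | −0.037 / −0.029 | −0.035 / −0.027 | −0.052 / −0.041 | −0.094 / −0.085 |

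Worked cell, extreme case at 2%: L-PRF leaks 0.05×171.5 + 3.5 = 12.08 of 175 (6.90%). Control leaks 0.063×171.5 = 10.80 of 175 (6.17%). Difference in success 6.17% − 6.90% = −0.0073. SE = √(0.0690×0.9310/175 + 0.0617×0.9383/175) = 0.0264. Lower limits: −0.0073 − 1.96×0.0264 = −0.059 and −0.0073 − 1.645×0.0264 = −0.051.

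**4. Reading.** With no data missing, the planning rates give −0.035 (95%) and −0.028 (90%). The extreme case stays inside the margin at 1% missing and crosses it on both limits at 2%. Counting every missing outcome as a leak in both arms crosses only the 95% limit, and only near 5%. Complete cases and all-success barely move the limit.

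**The case against.** The best defence is that the outcome is largely captured without a visit. Section {12} defines a relevant leak by what it triggers, such as revision, puncture, a longer stay or repeat imaging, and takes complications from hospital databases. Section {18a} draws inpatient and outpatient data from electronic files, and Table 2 has leak assessments at FU1 and FU2 as well as FU3. This is a plausible basis for expecting few missing outcomes, and it stands. What remains are patients who withdraw, for whom {11b} ends collection, and leaks treated elsewhere.

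Several stronger readings are tempting but not supported:

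- **Missing outcomes nearly as numerous as leaks.** The 2–5% also covers non-adherence and failed L-PRF preparation, and leak status can still be observed in those patients. Missing outcomes are therefore a subset of unknown size, and even the full figure is only about a third of the expected leaks at 2%.
- **Default handling favours non-inferiority.** That requires missingness related to leakage differently in the two arms, and nothing in the article shows this.
- **A failed telephone call means a missing primary outcome.** The call concerns questionnaires. A patient labelled lost under {18b} may have a known leak status in the record. The fault is that one label covers two different losses.
- **The lack of an imputation method is itself a defect.** Such methods are often left to an analysis plan, which is not shown. The point rests on a statement that other sections contradict and on a check that cannot do what it claims.
- **Within-arm multiple imputation is needed.** Without informative covariates it reproduces the complete-case estimate on average and adds little.

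**Conclusion.** The point stands as a contradiction between {20c} and sections {14} and {11b}, together with a stated check that does not address missing outcomes. Its size is bounded, not known: at most 7 to 17 missing outcomes against about 20 expected leaks, and probably fewer. An extreme allocation of 2% missing is enough to lose non-inferiority on either the 95% or the 90% limit, while at 1% it is not. These limits assume the planning rates, equal losses between arms and Wald intervals. The extreme case is a bound, not a forecast. The handling of unknown leak status could decide the conclusion, so it should be fixed before allocation is revealed to the analysts.

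**What to change.** - Delete the sentence in {20c} and reconcile {11b}, {14}, {18b} and {20c}.
- State that leak status is sought from the hospital record for every randomised patient, and add a leak question to the existing FU3 telephone call.
- Define loss for the primary endpoint separately from loss for the questionnaires.
- Ask withdrawing patients whether outcome capture from their records may continue.
- State how a randomised patient with unknown leak status is counted under intention-to-treat.
- Add a tipping-point table showing how many missing L-PRF outcomes would have to be leaks, for a given handling of missing controls, before non-inferiority is lost. Stop presenting the comparison of the three analysis sets as the missing-data check.

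The cost is an amendment, which under {25} goes to the Ethical Committee, one extra question on a call already made, and minor analysis work. Recruitment began in January 2020, so the call question cannot reach patients already followed up. For them the record search is the available source.

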## Trial design {8}

This study is a single-blinded, prospective randomized controlled trial with subjects randomized 1:1 in two parallel groups, i.e., experimental (L-PRF treatment) and active control (commercially available fibrin sealants).

In this study, the general objective is to show the non-inferiority of L-PRF as a closure technique compared to commercially available fibrin sealants in supra- and infratentorial surgery. This prospective randomized controlled trial was approved by the local Ethical Committee (UZ Leuven, S61460) and is registered at ClinicalTrials.gov (ID: NCT03812120) [2]. Recruitment started on 06 January 2020.

Demographic data, medical history, and surgical indications are reported prior to surgery. During the hospitalization (from 1 day preoperatively until the day of discharge), vital parameters such as body temperature and blood pressure are monitored, as well as medication intake. Patient’s quality of life (QoL) is questioned using the Research and Development 36-item Short Form Survey (RAND SF-36) and EuroQol Five Dimensions (EQ-5D) questionnaires.

To perform a cost-effectiveness evaluation, all costs and effects will be collected. Additionally, patient’s general quality of life is assessed using the EQ-5D-3L Questionnaire prior to surgery and at the 6–12 weeks follow-up visit (FU3). Complications and adverse events are assessed at the time of surgery, 2 days postop (FU1), at hospital discharge (FU2), and at follow-up visits (FU3) (Fig. 2).

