For the cost-effectiveness analysis, the “healthcare payer” perspective will be adopted, which means that all direct treatment-related costs as well as costs related to follow-up will be included in the analysis. For the cost analysis, the following outcomes will be considered: used materials during surgery (units), surgery duration (minutes), intensive care hospitalization time (days/hours), duration of hospitalization (days), associated facility, and staff resources. These data will mainly be retrieved from the hospital records and requested at the hospital’s billing office, if necessary. The most recent unit prices at the time of analysis will be applied. Depending on the primary outcome, i.e., the effectiveness of dural closure, and the clinical effects of both treatments, analysis will be performed as cost-utility or as cost minimization [11, 12]. In addition, the use of EQ-5D-3L to calculate QALYs at 6–12 weeks postoperative will be explored to compare EQ-5D utility scores to other outcomes described above.

The outcomes will be assessed at five study visits within a timeframe of twelve postoperative weeks (Table 2), and a comparison will be made between the two groups considering the change to baseline. Data will be presented as mean and standard deviation or median and interquartile range for continuous variables (including body temperature, °C; blood pressure, mmHg; diameter of craniotomy, mm) and as proportions with 95% confidence intervals for categorical variables (complications, surgical indication, surgical approach). Baseline medical characteristics will be compared between the allocation groups in a similar fashion.

**Table 2 Tab2:** Outcome assessment

Procedure	Visit 1: *screening*	Visit 2: *allocation*	Visit 3: *FU1*^a^	Visit 4: *FU 2*^b^	Visit 5: *FU 3*^c^

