#### Adverse events reporting and harms {22}

Harms and adverse events that may be expected in the study population include intracranial hemorrhage, tension pneumocephalus, wound problems, and neurologic complications such as seizures, dysphasia, or motor deficits [15]. During hospitalization, harms will be systematically collected from documentation of clinical and radiological examinations and daily nursing reports in the electronic patient files. At the outpatient follow-up (FU3), harms will be collected based on anamnesis and clinical examination. Additionally, four open-ended questions will be presented to the subjects:

Did you suffer from any complaints?Have you been ill?Have you taken any medication?Were there any problems regarding wound healing?

During the study, all adverse events are recorded and notified to the sponsor with a yearly progress report. According to the local law, serious adverse events are reported immediately, after first knowledge, to the sponsor, accompanied by detailed written reports. A serious adverse event is defined as any untoward medical occurrence or effect that results in death, is life-threatening, requires hospitalization or prolongation of existing hospitalization, results in persistent or significant disability or incapacity, or is a congenital anomaly or birth defect. Serious adverse events defined as such will be reported in the final manuscript of the study. The sponsor shall keep detailed reports of all adverse events which are reported. For the reported death of a subject, the investigator shall supply the institutional Ethical Committee with any additional information requested.

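### The within-arm mean rule for missing cost-effectiveness values has no exception for death, so a patient who dies before FU3 is given survivors' EQ-5D utility

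*Protocol article*

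**What the plan says.** Trial design {8} and Table 2 of the protocol article place EQ-5D at two points only, before surgery and at FU3. A patient who dies between them has no postoperative EQ-5D.

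On its use, Outcomes {12} says that "the use of EQ-5D-3L to calculate QALYs at 6–12 weeks postoperative will be explored". It adds that, depending on the primary outcome and the clinical effects, "analysis will be performed as cost-utility or as cost minimization".

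Section {20c} defines the intention-to-treat set as "all randomized participants, irrespective of protocol adherence" and gives one rule for missing economic data: "For secondary endpoints (cost-effectiveness evaluation), the predictive mean of the other values within the arm will be used".

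Section {18b} covers the patient who does not attend FU3 in the window and is then telephoned for the questionnaires: "If this attempt is unsuccessful, the patient is considered lost to follow-up". It has no separate category for a patient who has died.

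Death is foreseen in {22}, where a serious adverse event includes "any untoward medical occurrence or effect that results in death, is life-threatening". No section assigns death a utility or takes it out of the imputation.

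**The concern.** A missing questionnaire from a living patient is an unknown value, and filling it is a matter of estimation. After a death nothing is unknown: on the QALY scale utility is 0 from that date. The rule in {20c} does not separate the two cases. At FU3 the other values in the arm can come only from patients alive to answer, so the rule puts survivors' health in place of a known 0.

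This is an error in the value itself, separate from the understated variance of single imputation. Multiple imputation of the same cells would also draw on survivors. Comparing the three analysis sets in {20c} would not reveal it either, because a patient treated as allocated who then dies belongs to all three.

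At stake is the EQ-5D and QALY comparison. Under the rule, excess deaths in one arm cannot lower that arm's mean utility.

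**Working it through.** **Inputs from the protocol article.** 175 patients per arm (Sample size {14}); EQ-5D at screening and FU3; a 12-week horizon. The plan states no figure on this point that could be reproduced. The sample size that supplies the 175 does reproduce closely: 166 per arm computed against 167 stated, and 341 to 352 after 2–5% drop-out against 350. It does not otherwise bear on the point.

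**Assumptions.** The article gives neither a mortality rate nor a utility. I take mean survivor utility u = 0.7 to 0.9, equal in both arms, and death at week w = 1 to 6.

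**Step 1: mean FU3 utility in one arm.** With d deaths among n = 175:
- rule as written: arm mean = u
- deaths scored 0: arm mean = u(n − d)/n
- overstatement = u·d/n

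| Deaths in arm | u = 0.7 | u = 0.9 |
|---|---|---|
| 1 | 0.004 | 0.005 |
| 2 | 0.008 | 0.010 |
| 4 | 0.016 | 0.021 |
| 9 (about 5%) | 0.036 | 0.046 |

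**Step 2: QALYs over 12 weeks.** The excess per death is u(12 − w)/52. Divided by 175, it gives the excess per patient in the arm:
- central, u = 0.8, w = 2: 0.8 × 10/52 = 0.154; /175 = 0.00088
- low, u = 0.7, w = 6: 0.7 × 6/52 = 0.081; /175 = 0.00046
- high, u = 0.9, w = 1: 0.9 × 11/52 = 0.190; /175 = 0.00109

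**Step 3: the comparison between arms.** With equal survivor utility, the shift is u(d₁ − d₂)/175.
- equal deaths: 0
- 4 against 1: 3u/175 = 0.012 to 0.015
- 6 against 2: 4u/175 = 0.016 to 0.021

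In the last two cases a true deficit of that size in FU3 utility is shown as 0. Over 12 weeks by the trapezoid rule, 6 against 2 is worth u × 4/175 × 12/52 × 1/2, or about 0.002 QALY per patient.

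**The case against.** The strongest reply is that the article never calls a death missing data. Section {20c} is a missing-data rule, {18b} concerns living patients who cannot be reached, and {22} gives deaths their own route. Scoring death as 0 is routine detail that a health-economic plan, not shown here, could supply. This has force: the reading rests on an unqualified rule and not on an explicit instruction about deaths. It does not remove the point. The article commits to a rule, keeps all randomized patients and names no exception, so an analyst who follows the text fills the cell from survivors, and a later plan would have to qualify it. That the predictive mean is undefined does not help either, since a model-based version would still be fitted to survivors.

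The other side is right on scope, and four stronger readings that a reader might infer are not supported:

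- **That costs are also mis-scored.** Outcomes {12} takes resource use mainly from hospital records and, if necessary, the billing office. Those data do not depend on attending FU3.
- **That one death outweighs the whole non-inferiority margin in QALYs.** If a leak costs 0.2 utility for 4 weeks (assumed), the 5-point margin is worth 0.05 × 0.2 × 4/52 = 0.00077 QALY. The low end for one death, 0.00046, is below that. At 6 weeks per leak the margin is worth 0.00115, above the whole range for one death.
- **That a few deaths would decide the sign of net benefit.** This needs a willingness-to-pay value, which the article does not give. At an assumed EUR 40,000 per QALY, the central case is worth about EUR 35 per patient per death. Offsetting the material saving then takes about 3 excess L-PRF deaths at the low end (100 − 12 = EUR 88) and about 7 at the high end (250 − 12 = EUR 238). At EUR 20,000 it takes about 5 and 14.
- **That harm is hidden.** Section {22} has serious adverse events, including deaths, reported immediately to the sponsor and published in the final manuscript.

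**Conclusion.** The point holds as a small correction to a secondary, exploratory analysis. Read literally, {20c} gives a patient who dies before FU3 the utility of survivors. Each such death overstates the arm's mean FU3 utility by about 0.004 to 0.005, and its QALYs by about 0.0005 to 0.0011 per patient. These sizes rest on assumed survivor utilities of 0.7 to 0.9, death at weeks 1 to 6 and 175 per arm. None of the utility or mortality inputs comes from the document.

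The between-arm comparison is distorted only if deaths differ between arms, given similar survivor utility. If the economic evaluation becomes a cost minimization, QALYs do not enter its result. The primary endpoint is not affected.

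**What to change.** Add to {20c}: *Death is not missing data. For patients who die before FU3, EQ-5D utility is set to 0 from the date of death and QALYs accrue to that date. Imputation applies only to patients alive with a missing value.*

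Optionally, state in {18b} that a patient who has died is recorded as dead, with the date, and not as lost to follow-up.

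No new data collection is needed, because deaths are already reported as serious adverse events under {22}. The cost is a slightly lower mean utility and a larger variance in any arm with deaths. The wording should be settled before allocation is released, so that the choice cannot depend on the results.

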## Objectives {7}

The general aim of this study is to evaluate the potential of L-PRF in dural closure. More specifically, we are investigating L-PRF as an onlay graft on sutured dura in supratentorial and infratentorial surgeries. We aim to show the non-inferiority of L-PRF compared to the current standard practice. In addition, we want to demonstrate that L-PRF is more cost-effective than standard commercially available fibrin sealants. Risk factors and possible complications will be evaluated to validate safety.

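### Filling missing cost-effectiveness values with one predicted mean per arm understates standard errors; as a lesser point, the type of economic analysis depends on the observed results

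*Protocol article*

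**What the plan says.** Three places in the protocol article bear on this.

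- Objectives {7} makes the economic claim an aim of the trial: "we want to demonstrate that L-PRF is more cost-effective than standard commercially available fibrin sealants".
- The section on non-adherence and missing data {20c} expects no missing data for the primary endpoint. For the economic evaluation it says: "For secondary endpoints (cost-effectiveness evaluation), the predictive mean of the other values within the arm will be used". It names no multiple imputation, no added residual variation and no bootstrap.
- Outcomes {12} leaves the form of the evaluation open: "Depending on the primary outcome, i.e., the effectiveness of dural closure, and the clinical effects of both treatments", the "analysis will be performed as cost-utility or as cost minimization". No decision rule follows. On utilities it says only that "the use of EQ-5D-3L to calculate QALYs at 6–12 weeks postoperative will be explored".

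The one figure that bears on missingness is in Sample size {14}: "A drop-out rate of 2–5% is expected due to loss of follow-up and non-adherence to the allocation or failure of L-PRF preparation". No rate is given for missing EQ-5D or cost items.

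**The concern.** A single deterministic fill-in does two things to a standard error. The filled values add no spread, so the variance estimate shrinks. They are also counted as observations, so the divisor is too large. Intervals for the cost, EQ-5D and QALY differences are then narrower than the data justify, and those intervals would support the claim that L-PRF is more cost-effective.

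The second issue is separate and smaller. Cost-minimization compares costs alone, on the premise that effects are equal. If that route is chosen after the results are seen, an uncertain difference in effect is set to zero, and its uncertainty does not reach the cost-effectiveness conclusion.

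**Working it through.** **The plan's own figure.** The article gives no figure for the economic analysis, so the sample size is the only one to reproduce. Inputs from Sample size {14}: control success 93.7%, L-PRF success 95%, margin 0.05, one-sided alpha 0.05, power 80%. By the normal approximation:

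n per arm = (0.937×0.063 + 0.95×0.05) × (1.645 + 0.842)² / (0.013 + 0.05)² = 165.9, so 166 per arm and 332 in total.

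The article states 334 (167 per arm). The two agree to within 2 patients.

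**Effect of filling with the arm mean.** Take N = 175 randomized per arm, of whom m are observed, with values missing completely at random.

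- The point estimate is unchanged, since the filled arm has the mean of its observed values. Its correct standard error is s/√m.
- The standard error computed from the filled data is s × √[(m−1)/(N−1)] / √N.
- The ratio of computed to correct is √[((m−1)/(N−1)) × (m/N)], or about 1 − f for a missing share f.
- Coverage of a nominal 95% interval is 2Φ(1.96 × ratio) − 1, and the two-sided error is the remainder.

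| Missing share | m | SE ratio | Coverage | Error of nominal 5% test |
|---|---|---|---|---|
| 2% (low end of stated drop-out) | 172 | 0.983 | 94.6% | 5.4% |
| 5% (high end of stated drop-out) | 166 | 0.948 | 93.7% | 6.3% |
| 10% (assumed) | 158 | 0.903 | 92.3% | 7.7% |
| 20% (assumed) | 140 | 0.799 | 88.3% | 11.7% |

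A simulation with skewed (lognormal) costs and 4,000 runs per setting gave coverage of 94.7, 94.0, 92.1 and 88.6% in the same four rows.

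**If the value is a regression prediction.** With one covariate and an assumed correlation of 0.5, simulated coverage was 93.9% at 5% missing and 90.2% at 20%. The loss is slightly smaller at 20%, but the fault is the same.

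**Precision on effect.** At 167 per arm under the planning rates, the SE of the success difference is √[(0.937×0.063 + 0.95×0.05)/167] = 0.0253. The 95% half-width is 1.96 × 0.0253 = 0.0495, about 5 points, which is as large as the margin. If L-PRF were truly 2 points worse, non-inferiority would still be declared in about 28% of trials at one-sided 0.05. A non-inferior result is therefore not evidence of equal effect.

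**What cost-minimization leaves out.** Compare the SE of the cost difference with that of incremental net benefit:

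ratio = SD_C / √[(λ·SD_Q)² + SD_C² − 2λρ·SD_Q·SD_C]

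All inputs are assumed: λ EUR 20,000–40,000, QALY SD 0.03–0.05, cost SD EUR 3,000–8,000, correlation 0 to −0.3. The ratio runs from 0.74 (40,000; 0.05; 3,000; −0.3) to 1.00 (20,000; 0.03; 8,000; 0). Where cost variation dominates, the omission makes little difference.

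**The case against.** Much can be said for the plan, and part of it stands.

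- *The term is ambiguous.* The predictive mean could be a loose name for the arm mean, a regression prediction, or shorthand for predictive mean matching. Matching within multiple imputation would be sound. But the text names neither matching nor repeated imputation, and both deterministic readings share the fault. What stands is that the plan cannot be said flatly to ignore covariates; that holds only if the arm mean is meant.
- *Missingness may be low.* Costs come mainly from hospital records, with the billing office as back-up, and missed questionnaires are followed up by telephone. Part of the 2–5% is non-adherence or failed preparation, which need not mean missing data. This stands, and it keeps the size small on the document's own figures.
- *Imputation detail belongs in an analysis plan.* That would answer a complaint of omission. Here a method is named, and the method is the problem.
- *Cost-minimization.* A reader might infer that it too gives over-narrow intervals. It does not narrow the interval for the cost difference; it leaves out the effect term. A reader might also infer that meeting the 5-point margin triggers it. Outcomes {12} gives no such rule and refers also to the clinical effects of both treatments.
- *Break-even cost of a leak.* From the Background prices one can compute that a material saving of EUR 88–238 (100 − 12; 250 − 12) is cancelled at a 5-point excess of leaks once a leak costs more than EUR 1,760–4,760 (88/0.05; 238/0.05). This is no case against cost-minimization. Outcomes {12} includes treatment-related and follow-up costs, so recorded leak costs would still enter the cost difference. Only the health loss would be left out, and the document offers no figure for it.

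**Conclusion.** The imputation point holds. Followed as written, the rule treats filled values as data and understates the standard errors, for the arm mean by about the missing fraction. If missingness equals the stated 2–5% drop-out, the SE is 1.7–5.2% too small and a nominal 5% test has 5.4–6.3% error. The 7.7–11.7% range needs 10–20% missing, which the document does not suggest. These figures assume values missing completely at random and 175 per arm.

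A reader might go further and conclude that the cost-effectiveness objective would be met by artefact. The documents do not support that: the inflation is slight at their own drop-out rate, and the QALY calculation is exploratory.

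The results-dependent choice of economic analysis is a lesser, separate point. The fault is the lack of a fixed rule, together with a route that assumes an equality of effect this trial is not precise enough to show. Both points concern a secondary objective and leave the primary non-inferiority test as it is.

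**What to change.** 1. In the missing-data section {20c}, replace the single predicted mean by multiple imputation carried out separately by arm and combined with Rubin's rules. Predictive mean matching would suit, using data already collected, such as baseline EQ-5D and SF-36, surgical approach, length of stay and leak status.
2. In Outcomes {12}, state that incremental cost and incremental effect are always reported with their joint uncertainty, for example by bootstrap, whatever the primary result. Cost-minimization need not be removed; it can stay as a supplement.

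The cost is revised wording, a modest amount of extra analysis in software other than GraphPad Prism, and slightly wider intervals. No further patients, visits or data items are needed.
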